**Figure 3. F0003:**

Participants’ timeline (CID – clinical investigation day).

### Eligibility criteria

*Inclusion criteria*: age between 18 and 65 years; running for no longer than 3 months; performing a minimum of 60 min of vigorous physical activity per week; being free from major orthopedic limitations (defined as those which would limit moderate to vigorous physical activity (MVPA)); and from clinical diagnosis with any condition that may interfere with performing MVPA; being free from untreated or major psychological disorders (e.g. psychosis, clinical depression); and possessing or willing to acquire a smartphone or computer with internet access.

*Exclusion criteria*: inability to provide written informed consent; inability to follow written material or telephone conversations in Portuguese that would preclude completion of study questionnaires and use of the digital intervention (i.e. KOR toolkit, see below); intention of pregnancy in the next 12 months; planning to travel for more than 2 weeks in the next 12 months or to emigrate; suffering any injury in the course of the study.

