This paper describes the rationale, intervention development, study design, and pilot study of the Keep On Running (KOR) trial. KOR aims to test a brief theory-based intervention, delivered through digital technology (web app), targeting maintenance of recreational running behavior over time (i.e. relapse prevention) after being voluntarily initiated in the previous 3 months. The pilot study was focused on intervention adherence and participant satisfaction in order to establish the feasibility and acceptability of the intervention toolkit. Furthermore, it was also used to test the feasibility and acceptability of the questionnaires selected to be part of the later RCT.

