### Data collection

Participants will go through four assessment periods at baseline, 6 weeks (post-program), 6 months, and 12 months follow-up. The training and clarification session will be completed by telephone to ensure participants are equipped with the skills to access the intervention contents. Before the first, third and fourth assessment periods, eligibility will be checked against inclusion and exclusion criteria through a telephone screening/re-screening call, 1 week prior to each visit. Participant's timeline is shown in Figure 3.

*Assessment* 1 (baseline): Clarification session about the study. If participants are still interested in enrolling in the study, eligibility will be checked, and they will be asked to fill out an informed consent form. Randomization and allocation to one of the four arms of the trial will be performed. Data on demographics and potential psychological moderators will be collected. A battery of psychological and behavioral questionnaires will be completed online using google forms (in one-week time) – running behavior (i.e. frequency and minutes per week), motivations, basic psychological needs, motives and gains, self-regulation skills, passion, flow, and vitality. This task is estimated to take approximately 1 h, but participants will be able to do breaks and return later to complete the psychometric evaluation during that week. Debrief on how to use the KOR web-based intervention content – the toolkit (approximately 1 h).

*Assessment*s 2 and 3 (intervention's end and 6-month follow-up). Email reminder prior to this evaluation period will be sent. The same battery of psychological and behavioral questionnaires will be completed online using google forms (in one-week time) – running behavior (i.e. frequency and minutes per week), motivations, basic psychological needs, motives and gains, self-regulation skills, passion, flow, and vitality –, and will take approximately 1 h.

*Assessment* 4 (12-month follow-up). Running behavior maintenance will be assessed through a telephone call, asking participants whether they keep running at their initial level or higher, or not.

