#### Pilot program evaluation: participant satisfaction

Overall, participants understood the purpose of the study, the concepts underlying the questionnaires and the toolkit, and felt supported by the research team. Most participants (83.3%) found the questionnaire too long. Participants generally found the toolkit website to be attractive and user friendly, classifying their overall experience with the study as positive. Most of the interviewed participants already used a running monitoring app, so they found the program to be less intuitive, repetitive in some questions and missing out important aspects such as ‘time of day, speed/ pace, and altimetry’. Additionally, participants reported problems with platform adjustment that led to ‘information overlap when used on cellphone’, the fact that ‘it didn't keep data inserted in previous sessions’ and ‘errors in google docs that forced them to restart the questionnaire’.

Three participants suffered injuries during the intervention period (25%). Two had muscular running-related injuries in the lower limbs and one had a foot trauma injury while playing football.

This pilot study had limitations that need to be considered, Due to recruitment constraints, the final sample included long time runners, which may differ from beginners, targeted by the RCT protocol. The low sample size and the absence of follow-up hindered further interpretation about the efficacy of the toolkit as it is.

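### In-study injury is an exclusion criterion and eligibility is re-checked after randomisation, which can bias the comparison of running maintenance

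*Protocol article*

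**What the plan says.** Three parts of the protocol article bear on this.

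- **Eligibility criteria.** Entry requires "running for no longer than 3 months" and "performing a minimum of 60 min of vigorous physical activity per week". The exclusions end with "suffering any injury in the course of the study", with no limit on cause or severity.
- **Data collection.** At assessment 1, "Randomization and allocation to one of the four arms of the trial will be performed". The same section states: "Before the first, third and fourth assessment periods, eligibility will be checked against inclusion and exclusion criteria through a telephone screening/re-screening call", one week ahead of each. Assessments 3 and 4 fall at 6 and 12 months. Assessment 2, at 6 weeks, has no re-check.
- **Assessments.** The primary outcome is self-reported running (frequency and weekly minutes) at baseline, end of intervention and 6 months. At 12 months participants are asked by telephone whether they still run at or above their starting level.

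The article does not say what happens to a participant who fails the re-check. Nor does it say that such a participant is still assessed and analysed in the assigned group. The nearest provision, in Analytical strategy, is multiple imputation if necessary, and it does not mention people excluded after randomisation.

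**The concern.** Eligibility criteria define who enters a trial. Once they are applied after allocation, they define who stays, and what they test may by then have been affected by the allocated arm. Here two of the criteria are close to the outcome. Injury can stop someone running, and an intervention that changes running volume could change injury risk. Weekly vigorous activity overlaps with running minutes, which are the primary outcome. In a trial about preventing relapse, a gate that tests these items a week before the outcome is collected can lose the very people whose status the trial needs to record.

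What is at stake is the randomised contrast, SRM against no SRM within the organised (PNMC) and free (FRR) runners, at 6 and 12 months. The 6-week result escapes the re-check but is still exposed to the injury exclusion.

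**Working it through.** **1. Can the re-check operate as written?** Randomisation is at assessment 1. The calls before assessments 3 and 4 come about 6 and 12 months later, less one week. Set against the criteria:

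| Criterion | Status at the 6- and 12-month calls |
|---|---|
| Running for at most 3 months | Counted from when running began, failed by everyone |
| At least 60 min/week of vigorous activity | Failed by someone who stopped running and does little other vigorous exercise; met by someone who switched to another vigorous activity |
| No injury during the study | Failed by anyone injured since enrolment |

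The first row shows that the full list cannot be meant literally. The article does not say which part is.

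**2. The pilot injury figure.** The pilot results report three injured participants, stated as 25%. With the 18 enrolled, 3/18 = 16.7%. The stated 25% needs a denominator of 12, because 3/12 = 25%; the article does not name one. Either value, reached in 6 weeks, exceeds the 15% dropout allowance in Power calculations and sample size estimation.

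**3. Loss of participants if injury excludes.** Inputs: 55 per group, 220 in total, 15% dropout. Remaining = 55 × (1 − injury share), and × 0.85 with dropout added.

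| Injury share | Excluded of 220 | Left of 55, injury only | Left with 15% dropout as well |
|---|---|---|---|
| 0 (no such rule) | 0 | 55 | 46.8 |
| 16.7% (3/18) | 36.7 | 45.8 | 39.0 |
| 25% (as stated) | 55 | 41.3 | 35.1 |

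The last column assumes that injury and dropout are independent; if all dropouts are also injured, the injury-only column applies. The 35.1 is below the 37 per group that the article says it needs. I take that 37 as stated; whether it is right is a separate question.

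**4. Selection on relapse (illustration).** The article gives no maintenance rates, so assume true 12-month maintenance *p* of 50% (control) and 60% (SRM). If a share *e* of relapsers is screened out in both arms, observed maintenance = *p* / (1 − (1 − *p*)*e*).

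| *e* | Control | SRM | Difference (points) |
|---|---|---|---|
| 0 | 50.0% | 60.0% | 10.0 |
| 0.5 | 0.50/0.75 = 66.7% | 0.60/0.80 = 75.0% | 8.3 |
| 0.7 | 0.50/0.65 = 76.9% | 0.60/0.72 = 83.3% | 6.4 |
| 0.9 | 0.50/0.55 = 90.9% | 0.60/0.64 = 93.8% | 2.8 |
| 1.0 | 100% | 100% | 0 |

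The article does not determine *e*, and it could be 0.

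**5. Selection on injury (illustration).** Assume that 60% of uninjured runners maintain in both arms, that no injured runner does, and that injury shares are 17% and 25%. Among all randomised, maintenance is 0.60 × 0.83 = 49.8% and 0.60 × 0.75 = 45.0%, a gap of 4.8 points. With the injured excluded it is 60% in both arms, a gap of 0. If SRM has more injuries, exclusion hides a 4.8-point disadvantage and so favours SRM. If the control group has more, it hides a 4.8-point benefit. The bias can go either way.

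**The case against.** The strongest reply is that the article says eligibility will be checked, not that those who fail are withdrawn. The 12-month question expects some participants to report that they have not kept up their running, which suggests that relapsers are meant to be reached. Since the three-month criterion would fail everyone, the intended re-check may cover health items only. The pilot also followed procedures equivalent to the RCT's, apart from randomisation. Three pilot participants were injured, and three dropped out for reasons that included lack of time as well as injury. At least one injured participant therefore probably finished the intervention, which speaks against automatic removal. Finally, the handling of withdrawals often sits in a full protocol or SAP that is not shown.

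Much of this stands, and it limits the point. Three stronger readings are tempting but not supported:

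- *Relapsers are removed.* This is an inference from re-checking the activity criterion; the article never states it.
- *Maintenance is guaranteed among those who remain.* It is not. The criterion is vigorous activity, not running, and 94.4% of pilot participants did other exercise. The 12-month outcome is relative to each person's own starting level, so someone can pass 60 minutes and still have cut back.
- *The pilot injury rate can be projected to 12 months.* That would rest on three events in 6 weeks, in runners averaging 6.3 years' experience, with one injury from football. The article itself warns that they may differ from beginners.

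The reply does not remove the core. In-study injury is explicitly an exclusion, the re-check is explicitly against the criteria and after randomisation, and nothing in the article keeps those who fail in follow-up. This is a stated rule rather than an omitted detail, and an analysis plan cannot recover outcomes that were never collected.

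**Conclusion.** The point holds in a limited form. The injury exclusion is explicit and conditions the sample on an event after randomisation that is tied to the outcome. The re-check at 6 and 12 months is unworkable as written, and its consequence is undefined. It may lose some participants who stopped running, but how many, if any, cannot be known from the article.

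The only size the article itself supports is the pilot injury share, 16.7% (or 25% as stated) in 6 weeks against a 15% dropout allowance. If injury excluded at those shares, a group of 55 would fall to 45.8 or 41.3 before other dropout. Applying pilot rates to beginners is itself an assumption. The maintenance illustrations rest on assumed rates and show mechanism and direction, not an expected bias.

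**What to change.** Amend Eligibility criteria and Data collection as follows:

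- Apply the inclusion and exclusion criteria once, before randomisation.
- Remove in-study injury as a reason for exclusion from follow-up or analysis.
- Keep the 6- and 12-month calls as reminders, not as a condition for outcome assessment.
- Collect outcomes from everyone randomised and analyse them in the assigned group, using the running actually reported after an injury. A fixed score for injured runners is not needed; it would be a separate and debatable choice of estimand.
- Record injury by arm as an event. Keep an analysis without injured runners as sensitivity only.
- Correct the pilot injury percentage or state its denominator.

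Whether an injured participant continues the intervention is a separate matter. The investigators should reconcile it across Eligibility criteria, Data collection, and the discontinuation statement in Ethics and dissemination.

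The cost is a short amendment and no new procedure, because the calls are already planned. The downside is a somewhat noisier outcome, since injured participants who run less stay in the comparison.

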### Motivation and self-regulation intervention

We developed a web-based intervention adapted from the motivational and self-regulation arm of the NoHoW tria (Marques et al., 2020; Scott et al., 2019). It consists of 11 short sessions divided in 8 modules with motivational and self-regulation based exercises, quizzes, videos and animations aimed to elicit reflection about motives, goals, barriers and strategies to foster running behavior sustainability. Beyond the long-term promotion of running behavior, by implementing theory-based and evidence-based behavior change techniques, this brief intervention aims at promoting participants’ intrinsic and well-internalized motivations for running and the use of self-regulation skills (e.g. goal setting) that facilitate behavior maintenance.

The intervention includes:
Access to a web-based intervention comprising 11 distinct sessions of 5–10 min each and 8 educational modules concerning motivation and self-regulation constructs, delivered through several technological implementations, including videos, animations, quizzes and exercises, as well as images, text and audio (Figure 4). Several multimedia tools, including a web-based HTML5 interactive map as a navigation tool for the SRM sessions (http://leafletjs.com/), the questionnaires platform to design interactive features, and whiteboard drawings to convey some of the more theoretical constructs of the intervention (http://www.videoscribe.co/), were used to develop these implementations, supported by the team's previous experience in similar interventions.Bi-weekly text messages (see Table 1 for an overview of weekly text messages to participants) are sent to prompt participants toward the sessions and each week specific contents. Yet, participants are able to move faster or slower through the program to fit their needs and availability.

**Figure 4. F0004:**
[figure not shown]
Screenshots of the intervention toolkit.

**Table 1. T0001:** Overview of weekly text messages to participants.

Text reminder 1	Good afternoon runner, you have already registered on the website http://kor.fmh.ulisboa.pt/. By now, you will have received an email to validate your account. Good races!
Text reminder 2	Good morning Athlete, have you had the opportunity to explore the contents and activities of the KoR program? Good Sunday wishes.
Text reminder 3	Good morning Athlete, how about a visit to the KoR program during today? This is the third of 11 reminders. Good races
Text reminder 4	Good morning Athlete, how is the exploitation of KoR content RUNNING? Good races
Text reminder 5	Good afternoon Athlete, you can do the activities of the KoR program at your own pace. How's your run going? Good races
Text reminder 6	Good afternoon Athlete, fortunately tomorrow is already cooling. We have now spent half of the KoR program. We hope you’re enjoying it. Good runs (in the shade)
Text reminder 7	Good afternoon, this is the 7th of 11 messages. At this point, you may have finished exploring the content or just be at the beginning. You can continue to enjoy content at your own pace. Good races
Text reminder 8	Good morning, the heat returned and we are on the final stretch of the KoR program. On vacation or at work we hope you are enjoying the program and your races. Good races
Text reminder 9	Good afternoon athlete! It is now just a little bit to finish your trip in the KoR toolkit. I hope you’re enjoying it. Good races
Text reminder 10	Good morning athlete! Weekend it is here, and a nice time for a run. This is the penultimate sms of the KoR program. You have certainly had the opportunity to explore the contents of the toolkit and reflect on your run. Best wishes for a great weekend
Text reminder 11	Good afternoon athlete! This will be the last message / reminder to access the KoR program. During this week, you will also be able to access the contents and register your race. Soon I will send you the link to complete the completion questionnaire. Have a nice week and good races

The SRM intervention includes both motivation and self-regulation components. The intervention's theoretical logic model is adapted from the NoHoW project (Marques et al., 2020; Scott et al., 2019) and presented in Figure 1. The self-regulation skills component will seek to empower users to identify goals and make action plans for when, where, and how the goals will be implemented, allowing them to formulate explicit implementation intentions. Coping plans for relapses will also be supported. The motivational component is therefore based on SDT and configured to optimally support participants’ psychological needs for autonomy, competence, and relatedness, via specific technological implementations (e.g. self-awareness exercises, videos and practice modules), and as a result improve autonomous regulation of physical activity behaviors. Participants will explore personal motives to run, skills, life goals, social connections, and other motivational elements. Messages, videos, animations, self-awareness questionnaires, among other tools, will stimulate users’ sense of volition and ownership (vs. external pressure), confidence and competence (vs. unpreparedness and sense of failure), and positive social support (vs. isolation). It is anticipated that the use of these implementations will increase autonomous self-regulation and intrinsic motivation, which are associated with longer-term behavior change, and positive health outcomes.

The SRM web-based toolkit will be accessible only to the groups receiving the SRM intervention. In addition, all the study participants will receive weekly email messages with general technical information about running. An individual telephone session will introduce runners to specific elements of their unique intervention and how it will unfold.

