### Recruitment and randomization

Part of the runners will be recruited from the PNMC program, which consists in 2–3 supervised running group-sessions of 10–20 runners per week, lasting 90 min each. Certified trainers lead these sessions, apply specific methodologies for running and for walking sessions. Prior to their enrollment, trainers must complete a training course. The other set of runners (which run freely, on their own) will be recruited from the community (recreational runners). To recruit this sample, we will use online advertisement and running events list servers, reach out for running clubs, and partnerships with both state and private organizations.

We will use a rolling recruitment strategy: participants will join the study as soon as they are considered eligible to facilitate management of available human resources. Each set of runners will be randomly assigned to the KoR intervention group or the control group general information group in a 1:1 ratio, stratified by group (PNMC and FRR). The method of randomized permuted blocks will be used, with random block lengths (4 or 6) (Broglio, 2018). Because participants will know which arm of the study they are in, blinding is not possible.

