### Assessments

Data on demographics (age, gender, date of birth, education, income, employment, marital status, weight, height, physical activity history, and personal characteristics) and potential psychological moderators (i.e. index of autonomous functioning) will be collected only at baseline.

The primary outcome of this study is running behavior, which will be measured at baseline, intervention's end and 6-month follow-up by self-report (frequency and minutes of running per week). At 12 months, participants will be asked by telephone whether they keep running (at least) at their initial level, or not.

Secondary outcomes will include putative mediators and outcomes. Basic psychologic need satisfaction will be assessed via the Psychological Need Satisfaction in Exercise Scale (Wilson, Rogers, Rodgers, & Wild, 2006); Basic psychological need frustration will be assessed trough the Basic Psychological Need Frustration in Exercise Scale (Chen et al., 2015); Motives and gains via Exercise Motives and Gains Inventory (Ingledew, Markland, & Strömmer, 2014); Behavioral regulations will be assessed via the Behavioral Regulation in Exercise Questionnaire – 3 (Cid et al., 2018); Self-determination trait will be assessed via the Index of Autonomy Functioning (Weinstein, Przybylski, & Ryan, 2012); Self-regulation skills will be measured trough the Action planning, Coping planning, and Action control scales (Sniehotta, Scholz, & Schwarzer, 2005a; Sniehotta, Schwarzer, Scholz, & Schuz, 2005b); Self-efficacy will be assessed via the Modified Bandura's Exercise Self-Efficacy Scale (Bandura, 1997); Automaticity will be measured trough the Self-Report Behavioural Automaticity Index (Gardner & Tang, 2014; Gardner, Abraham, Lally, & de Bruijn, 2012); and exercise identity via the Exercise Identity Scale (Anderson & Cychosz, 1994). Regarding psychological outcomes, flow will be measured through the Dispositional Flow Scale – 2 in Exercise (Jackson & Eklund, 2002); Vitality will be assessed through the Subjective Vitality Scale (Ryan & Frederick, 1997); and passion through the Passion Scale (Cid et al., 2019).

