#### Pilot participant characteristics

The CONSORT diagram for the pilot is shown in Figure 5. In total, 18 participants were enrolled and completed the baseline assessment. Of those, 3 dropped out during the intervention, allegedly due to time constraints and injuries; 15 participants finished the 6 week-intervention, 7 the post-program questionnaire, and 14 the overall study satisfaction questionnaire.

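### Text reminder 11 gives SRM participants an extra advance notice, apparently of the 6-week questionnaire, that is not described for the other arms (minor)

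*Protocol article*

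**What the plan says.** The section on the motivation and self-regulation intervention lists text messages among the intervention's components. They "are sent to prompt participants toward the sessions and each week specific contents". Table 1 gives 11 such texts. The last one is mainly a final reminder to use the program, and it adds: "Soon I will send you the link to complete the completion questionnaire".

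The same section restricts the material that the texts point to: "The SRM web-based toolkit will be accessible only to the groups receiving the SRM intervention". The contact it describes for everyone is by email: "all the study participants will receive weekly email messages with general technical information about running".

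For the post-program and 6-month assessments, Data collection says: "Email reminder prior to this evaluation period will be sent". It names no arm. It places telephone re-screening calls before the first, third and fourth assessments, but not before the second.

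Assessments defines the primary outcome as "running behavior, which will be measured at baseline, intervention's end and 6-month follow-up by self-report (frequency and minutes of running per week". At the end of the intervention it is collected in the online questionnaire battery.

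On response in the single-arm pilot, the article reports: "15 participants finished the 6 week-intervention, 7 the post-program questionnaire". Fourteen participants completed a separate satisfaction questionnaire.

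**The concern.** A notice that a questionnaire is coming belongs to data collection. Here it sits inside a message that is part of the experimental treatment. In a single-arm pilot this has no consequence. In a randomised comparison, one side of the contrast may be prompted to respond slightly more often than the other.

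If the extra notice changes who returns the 6-week questionnaire in the SRM arms, the responders being compared differ by selection as well as by treatment. The outcome is self-reported, participants know their arm, and the planned effect is small (d = 0.23). An avoidable difference in how the outcome is obtained is therefore worth removing. Multiple imputation, which the Analytical strategy foresees if necessary, would repair such a difference only under its missing-data assumption.

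**Working it through.** The plan states no response rate by arm, so there is no figure to reproduce. The check is a comparison of who is told what before the 6-week assessment.

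| Contact before the 6-week questionnaire | SRM arms | Other arms |
|---|---|---|
| Weekly email on running technique | yes | yes |
| Email reminder before the assessment | yes | yes (no restriction by arm) |
| Telephone re-screening call | not described | not described |
| Text announcing a questionnaire link (text 11) | yes | not described |

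The last row is the only difference in questionnaire notices. Two steps in reading it are inference:

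1. *That the other arms get no such text.* This follows from the texts being listed as an intervention component and referring to a toolkit that only SRM participants can open. The article does not state it outright.
2. *That the questionnaire meant is the post-program battery.* Text 11 does not mention running behavior and carries no link. Timing supports the reading: if bi-weekly means two texts a week, 11 texts take 11/2 = 5.5 weeks, so the last falls just before the 6-week assessment. The pilot's separate satisfaction questionnaire remains a possible alternative.

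**Which time points are affected.** Only the 6-week assessment. No SRM text is described near the 6-month or 12-month assessments, and each of those is preceded by a telephone call.

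**What the pilot contributes.** Return of the post-program questionnaire was 7/18 = 38.9% of those enrolled (exact 95% CI 17.3% to 64.3%), or 7/15 = 46.7% of those who finished the 6 weeks (21.3% to 73.4%). Pilot participants followed the intervention path and had no comparison arm. The figure shows that response can be low; it says nothing about what the text does to response.

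**What a size would need.** Let p be the proportion responding in an arm, and g the mean of responders minus the mean of non-responders in SD units, taken as equal in both arms. The responders' mean exceeds the arm's true mean by (1 − p) × g. The distortion of the between-arm difference is then

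g × [(1 − p_SRM) − (1 − p_other)] = g × (p_other − p_SRM).

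The document gives neither the response difference attributable to one sentence of text nor g, and the sign of g is open. The result has no determinable size or direction.

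**The case against.** The strongest reply is that the actual assessment prompt is common to all arms. The email reminder carries no restriction, so the asymmetry is one sentence added to a shared prompt. That stands, and it is why the point is minor. A reader might infer that SRM participants are prompted while controls are not; the Data collection section contradicts that.

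Second, Table 1 reads like the pilot's script. It mentions the weather and vacations, whereas the RCT recruits on a rolling basis, and the Conclusion announces adjustments to the intervention and its delivery. The final RCT texts may well differ. This also stands, but the article gives no other script and presents this one as the description of the intervention, so the sentence could be carried over unnoticed.

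Third, arm-by-arm invitation logistics are commonly left to the full protocol, so silence about texts to other arms does not prove there are none. This is fair: the point concerns what is described, and does not assert that controls get no notice.

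Fourth, SRM participants also have ten other texts and the toolkit, so deleting one sentence leaves most of the difference in contact. True, but that contact is the treatment under test; an announcement of data collection need not be part of it.

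A reader might also infer a bias that is a sizeable share of the expected d = 0.23, by combining the pilot's 39% with an assumed gain in response and an assumed gap between responders and non-responders. The document supports neither assumption. The 39% comes from people on the intervention path, so it cannot serve as the rate without the text. The main trial also intends a shorter questionnaire and plans for 15% dropout.

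**Conclusion.** The point holds as a minor one. As described, SRM participants receive one additional advance notice, apparently of the post-program questionnaire, that is not described for the arms they are compared with. Questionnaire prompting at 6 weeks, a primary-outcome time point, could therefore differ slightly between randomised arms. Size and sign are unknown.

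This rests on three assumptions: that the texts go to SRM participants only, that the announced questionnaire is the post-program battery, and that the sentence is kept in the RCT. The first two are the natural reading and the third is open. The document does not show a bias in the primary outcome and gives no reason to expect one at 6 or 12 months.

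**What to change.** For the RCT, do one of two things:

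- delete the questionnaire sentence from text 11, leaving the email reminder as the common notice; or
- send the same questionnaire notice, by the same channel and at the same time from randomisation, to all four arms at 6 weeks.

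The first costs one edited line in Table 1. The second costs one short message per participant in the non-SRM arms, with the small downside of one neutral contact they would not otherwise have had. If the announced questionnaire is in fact a different form, such as the satisfaction questionnaire, naming it in text 11 would settle the matter. No change is needed at 6 or 12 months on this account.
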